One innovative approach to reduce the threat posed by TTIs is the use of pathogen reduction technology (PRT). This technology has been approved by the European Medicines Agency (EMA), and a Conformitè Europëenne (CE) Mark was obtained for Mirasol-treated WB in 2015. In brief, Mirasol PRT, developed by Terumo BCT, requires riboflavin to be mixed into a whole blood (WB) unit, which is then exposed to UV light (313 nm) for 1 h [13]. The chemical reaction between riboflavin and UV light prevents DNA and RNA replication. Disruption of nucleic acids occurs through two independent mechanisms: (1) UV light breaking bonds in nucleic acids and (2) photo-activation of riboflavin molecules interacting with nucleic acids, leading to electron transfer and irreversible modifications to specific functional groups of nucleic acids (e.g., guanine) [14–16]. Agents with nucleic acids, including viruses, parasites, and bacteria, or white blood cells, are inactivated or destroyed by varying degrees. In vitro, Mirasol PRT reduces the infectious load in treated WB for most pathogens by 99.9% [14–18]. Data have demonstrated Mirasol reduces parasites (*Trypanosoma cruzi* [19], *Babesia microti* [20], *Babesia divergens, Leishmania donovani* [21], and *Plasmodium falciparum* [22]), bacteria (*Yersinia enterocolitica*, *Acinetobacter baumannii*, and *Serratia liquefaciens* [17, 23]), and viruses (HIV, HBV, and HCV [17, 18, 24, 25]) by three to seven logs. Destruction of WBCs reduces the risk of transfusion-associated graft-versus-host disease (TAGvHD) and is comparable to using gamma irradiation [26]. Cells without nucleic acids, i.e., RBCs and platelets, suffer only minor cellular damage while plasma proteins are well preserved [27, 28].

A single-center randomized trial of 226 participants in Ghana evaluated if Mirasol-treated WB reduces transfusion-transmitted malaria (TTM) [29]. The incidence of TTM was significantly lower in the Mirasol-treated WB group (1/28 [4%] compared to standard group 8/37 [22%]; *p* = 0.039). This small trial did not assess other TTIs or adverse outcomes that can only be evaluated with larger and longer trials. The objective of the Mirasol Evaluation of Reduction in Infections Trial (MERIT) is to investigate whether Mirasol PRT can prevent TTM as well as six other TTIs, namely HIV, HBV, HCV, HEV, HHV-8, and bacteria in vivo.

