### Randomization

Patients for whom a transfusion has been prescribed are referred to the study team by the attending physician or nurse. Participants who meet the eligibility criteria are assigned in a 1:1 ratio to either the control or treatment group using permuted block randomization. Participants may only be enrolled and randomized once. Randomization occurs only after confirming both Mirasol and control WB are available. The start of study treatment is defined as the initiation of the first WB transfusion. Participants receive all transfusions in the designated arm for up to 10 weeks after randomization.

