**Fig. 2 Fig2:**
[figure not shown]
Donor blood and recipient evaluation

Individuals who require additional transfusions are followed as above as long as they receive the additional transfusions within the first 6 weeks of their initial transfusion (i.e., they will be evaluated at 48 h, day 7, and day 28 of both the first and any subsequent transfusions). The visits are combined if they fall within the same window. However, once the individual reaches week 10 from the initial enrollment and transfusion, their follow-up ends. If individuals require transfusion support for transfusions received after the first 6 weeks of study participation, they still receive study blood transfusions as per their randomization until study exit at 10 weeks but do not have additional follow-up visits. To encourage adherence to study procedures, participants are compensated for their time and transportation for each scheduled visit. Participants are also eligible to withdraw from the trial at any stage.

In case of a transfusion reaction, the transfusion is stopped and the patient evaluated. After the relevant checks and investigations have been done, the transfusion may or may not be restarted. The participant’s trial arm is maintained for all future transfusions. Participating in the trial should not affect the usual patient care or require any alteration to concomitant medication.

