### Study power calculations

Table 1 shows the prevalence of TTIs contributing to the primary endpoint in donated blood and the expected number of infections per 1000 transfused participants in Uganda. We anticipate that participants will receive 1.5 units of WB on average [43] with ~ 50% of participants receiving at least two transfusions. Given the low infectivity of some TTIs, we further assume the risk of TTIs is independent of one another. We anticipate ~ 50% of transfusion recipients will have prior immunity to HHV-8 and HEV; in the absence of prior information, we hypothesize (conservatively) that immunity to these viral infections is independent. Under the above conditions, the expected cumulative incidence of at least one TTI by 10 weeks is 3.7% among control subjects (31 infections among 850 participants after factoring in 15% loss to follow-up). More specifically, we estimate that the 31 infections in the control arm will be comprised of 13 malaria (42%), 10 bacteria (31%), and 8 viral TTIs (26%). Because of uncertainties over the prevalence of disease in the donor population, the rate of infectivity, and 10-week return rates (conservatively ~ 15% LTFU expected), we have designed the study to enroll up to 2000 participants with 1000 subjects per trial arm over a 30-month period. There will be an interim analysis after 1000 study subjects have been enrolled. See stopping rules below.

**Table 1 Tab1:** Transfusion-transmitted infections in Uganda among blood donors. The table provides the prevalence of TTIs contributing to our primary endpoint in donated blood, sensitivity of screening methods (when used in Uganda), risk of a TTI given exposure to infected blood (i.e., infectivity), and the expected number of infections per 1000 transfused participants

Agent	Donor prevalence (%)	Screening method sensitivity (%)	Infectious units/1000 units of blood	Infectivity (%)	Expected number of infections/1000 transfused individuals+
HIV^#^	0.71	98	0.14	100	0.2
HBV^#^	2.41	98	0.48	75	0.5
HCV^#^	1.76	98	0.35	74	0.4
HEV*	0.6	No screening	6	75	6.8
HHV-8^	36.0	No screening	360	2.3	12.4
Malaria^∞^	5.0	No screening	50	20	15.0
Bacteria^≡^	1.5	No screening	15	50	11.3

^#^Seroprevalence data from Uganda Blood Transfusion Service in Kampala, Uganda, between April and June 2017

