*The primary endpoint* is the cumulative incidence of one or more TTIs by 10 weeks among the mITT population. Log-binomial regression models will be used to estimate the relative risk reduction of incident TTI by 10 weeks associated with the Mirasol PRT. If the log-binomial model fails to converge, a Poisson model with robust variance estimation will be specified. Individuals lost to follow-up (including those who miss one or more study visits) will be censored from the primary analysis. Sub-analyses will be conducted separately for adults and children (< 18 years) and by sex. The primary analysis will also be stratified by the number of transfusions, with participants who received 1–2 transfusions analyzed separately from those who received ≥3 transfusions. Stratified analyses will also be conducted by admitting hospital. Efficacy will also be analyzed at each follow-up visit.

Sensitivity analyses will be conducted to assess whether or not there were important differences in demographics or health status between those with and without complete follow-up. In the event there are differences between those lost to follow-up and those who completed all study visits, inverse probability censoring weighting and stratification will be used to assess potential selection biases [44]. Similar calculations will be made if there is differential follow-up. A sensitivity analysis will be performed among participants who completed their 10-week follow-up visit, regardless of any previously missed visits. An additional analysis will be performed restricted to participants who are negative for all bacterial, viral, and parasitic infections at baseline. A final sensitivity analysis will be performed among participants who attended at least one follow-up visit and test results for all TTI of interest are available. All analyses will be repeated in the ITT and PP populations.

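### The supplementary split of the primary analysis by transfusions received (1–2 vs ≥3) rests on a post-randomisation count, and the planning figures leave the upper stratum nearly empty

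*Protocol article*

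**What the plan says.** In the Analysis plan, after the log-binomial model for the primary endpoint, the article lists sub-analyses by age group and sex, then adds: "The primary analysis will also be stratified by the number of transfusions". The strata are fixed as "participants who received 1–2 transfusions analyzed separately from those who received ≥3 transfusions". Splits by hospital and by visit follow. The article attaches no caveat to the transfusion split and gives no reason for the cut at 3.

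The count is not known at baseline. Under Randomization: "Participants receive all transfusions in the designated arm for up to 10 weeks after randomization". Under Assignment of intervention, people transfused after week 6 keep to their arm: "they still receive study blood transfusions as per their randomization until study exit at 10 weeks".

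The Study power calculations give the expected exposure: "We anticipate that participants will receive 1.5 units of WB on average", with about "50% of participants receiving at least two transfusions".

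The section on statistical methods for baseline characteristics and safety outcomes plans a median number of transfusions per participant at the end of follow-up, summarised overall and by arm.

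**The concern.** Age, sex and hospital are fixed before allocation, so arms compared within them remain randomised groups. Transfusions received are different in kind, because they accrue while the participant is on the assigned product. The article leaves open several routes by which product could alter the count:

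- Haemoglobin change and acute reactions are listed under Intervention outcomes as between-arm comparisons, so equality is not assumed.
- A low haemoglobin is one of the stated grounds for transfusion at entry, so a smaller increment could plausibly lead to more transfusions.
- The Introduction acknowledges some effect on treated cells: "RBCs and platelets, suffer only minor cellular damage".
- A reaction can interrupt treatment: "In case of a transfusion reaction, the transfusion is stopped and the patient evaluated", and restarting is not certain.

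The plan's own arithmetic makes infection risk proportional to units. If arm shifted the count, the mix of one and two transfusions within the lower stratum, or of three and more within the upper, could differ between arms. That difference would pass directly into the stratum's relative risk.

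The second problem is the cut-point. The planning figures leave almost nobody above it, so the upper stratum could not show an effect even if its comparison were sound. What is at stake is that a non-randomised, sparse contrast is read as evidence of efficacy, or of its absence, at high exposure.

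**Working it through.** **1. Reproduce the plan's incidence.** Inputs are Table 1 (infectious units per 1000 × infectivity), 1.5 units per participant, and HEV and HHV-8 halved for 50% prior immunity. Expected infections per 1000 participants:

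- HIV 0.14 × 1.00 × 1.5 = 0.21
- HBV 0.48 × 0.75 × 1.5 = 0.54
- HCV 0.35 × 0.74 × 1.5 = 0.39
- HEV 6 × 0.75 × 1.5 ÷ 2 = 3.38
- HHV-8 360 × 0.023 × 1.5 ÷ 2 = 6.21
- Malaria 50 × 0.20 × 1.5 = 15.0
- Bacteria 15 × 0.50 × 1.5 = 11.25

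The sum is 36.97 per 1000. Combined as 1 − ∏(1 − p), this is 3.65%, and 0.0365 × 850 = 31.0. The stated 3.7% and 31 of 850 reproduce, so 1.5 is the exposure figure on which the plan rests. Power at 3.7% vs 0.74% with 850 per arm and two-sided 0.05 comes to 98.6% (pooled normal approximation), against the stated 97%. Neither figure uses the transfusion strata.

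**2. Size of the ≥3 stratum.** Let T be transfusions per participant. The ITT population, from which the mITT is drawn, requires at least one study transfusion, so T ≥ 1 and

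E[T] = 1 + P(T≥2) + P(T≥3) + P(T≥4) + …

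Hence P(T≥3) ≤ E[T] − 1 − P(T≥2).

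At face value this is 1.5 − 1 − 0.5 = **0**. The mean is given in units and the share in transfusions. Provided each transfusion uses at least one unit, E[T] is at most 1.5 and the bound only tightens.

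**3. Allow for rounding.** Assumed ranges are mean 1.45–1.55 and share with at least two 45–55%. Upper bound on P(T≥3):

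| Mean | 45% | 50% | 55% |
|---|---|---|---|
| 1.45 | 0 | not possible | not possible |
| 1.50 | 5% | 0 | not possible |
| 1.55 | **10%** | 5% | 0 |

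Where the table says not possible, the bound is negative and the two inputs cannot both hold.

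**4. Events and power in that stratum.** The risk range runs from the average 3.7% to 7.4%, which doubles the risk because three units are twice 1.5. Efficacy is 80%.

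- At 10%: 850 × 0.10 = 85 per arm. Control events are 85 × 0.037 = 3.1 to 85 × 0.074 = 6.3. Mirasol events are 0.6 to 1.3. Power is 26–47% by normal approximation and 6–30% by Fisher's exact test.
- At 5%: about 42 per arm. Control events are 1.6 to 3.1. Power is 15–26% by normal approximation and 0.3–5% by Fisher.

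**5. Longer-tailed distributions.** A 1 + Poisson count with 50% at two or more puts 15% at three or more, but its mean is 1.69, not 1.5. Holding the mean at 1.5, a 1 + Poisson count gives 9% at three or more and a geometric count gives 11%, but then only 39% and 33% have at least two. None of these meets both stated figures.

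**6. Bias.** The document gives no transfusion count by arm and no size for any arm effect on it, so no calculation is possible.

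**The case against.** The strongest reply is that little depends on this analysis. The word *also* places it among supplementary splits. The primary test is the unstratified log-binomial comparison, and neither its power nor the interim rule uses the strata. A reader might infer that the primary comparison is itself divided, or that its 97% power is lost. The text does not support that.

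Next, a reader might infer that Mirasol does change the number of transfusions. The document does not show this. It describes the cell damage as minor, leaves the decision to transfuse with the attending physician, and blinds the staff who transfuse and monitor. Measuring haemoglobin change is not evidence of a difference. This stands: an arm effect on the count is a possibility only.

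Third, the two problems pull against each other. If at most 10% lie at three or more, at least 90% lie at 1–2, and that stratum nearly repeats the randomised comparison. This is fair for the lower stratum. It does not rescue the upper one, which would be both selected and sparse. If the real tail is longer than planned, sparseness eases but selection matters more.

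Fourth, the planning figures are approximate. One might hold the mean at 1.5, move only the share to 45%, and conclude at most 5%. That is too tight, because both inputs are rounded and together they allow about 10%.

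Finally, transfusions received are the actual exposure to donor infection, which no baseline variable measures, and the planned median by arm already gives some check on imbalance. Both points stand in part. With about half at one and half at two or more, however, a median says little about the share at three or more.

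**Conclusion.** The point holds in limited form. The supplementary 1–2 vs ≥3 split conditions on a count that arises after randomisation and that arm could affect, so its within-stratum relative risks are not randomised comparisons. The size and direction of any bias are unknown, and the primary test is unaffected.

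The cut at 3 conflicts with the stated planning figures. They imply an upper stratum of 0% at face value and at most about 10% under generous rounding: up to about 85 per arm, about 3 to 6 control events, and at best under 50% power for 80% efficacy.

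This rests on the assumed rounding ranges, at least one unit per transfusion, 15% loss applied equally across strata, and risk between the average and twice it. The equal-loss assumption may be generous. Extra transfusions in the first six weeks can add visits, and missing any visit removes a participant from the primary analysis. A stratum that proves larger in practice would mean the planning mean or share was wrong. It would not make the comparison randomised.

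**What to change.** Change the Analysis plan wording as follows:

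1. State that the split by transfusions received is descriptive only and supports no inference about efficacy or a dose effect.
2. Cut at 1 versus 2 or more. On the planning figures that puts about 425 per arm in each stratum. With risk proportional to units, 3.7% ÷ 1.5 = 2.47% per unit, giving about 425 × 0.0247 = 10.5 control events at one transfusion and 425 × 0.0493 = 21.0 at two.
3. Report the mean and full distribution of transfusions by arm, in addition to the planned median.
4. If an inferential subgroup is wanted, define it by a variable recorded before randomisation, such as baseline haemoglobin, and test it with an arm-by-subgroup interaction.

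This needs no extra participants or data collection. The costs are that a cut at 2 no longer isolates the most heavily transfused, and that a baseline variable is an imperfect proxy for exposure. The distribution in item 3 will show how many participants reached three or more.

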#### Stopping rules

An interim analysis for efficacy with respect to the primary outcome (incidence of any study TTI) will be performed when 10-week outcome data are available for the first 1000 randomized transfusions. The Lan-DeMets implementation of the O’Brien-Fleming procedure will be used for this single interim analysis; the alpha level will be set to 0.00304, with the final testing alpha set at 0.04895 to maintain the overall alpha of 0.05 [45]. Under the protocol-specified efficacy of 80%, there is 49% power for this interim criterion to be met. If this criterion at 1000 is met, and at least 25% of the observed reduction is due to reduction in pathogens other than malaria, then stopping for efficacy may be recommended. A futility analysis will also be performed in the event the stopping rule is not met. Under the assumption that the future events are affected by the protocol-specified 80% reduction parameter, the conditional probability of the final *p*-value being less than 0.04895 will be calculated; if it is less than 10%, early termination may be recommended due to futility.

The Safety population will consist of all randomized subjects who undergo at least one study transfusion, independent of the outcome or successful completion of the procedure. Summaries by treatment group will be based on the treatment actually received. Specifically, the safety analyses will evaluate adverse transfusion reactions, delayed transfusion reactions, hemoglobin increments, treatment-related adverse events, and all-cause mortality. The trial might also be stopped if there are safety concerns.

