*HEV seroprevalence in Uganda is 47% [38]. However, RNA positivity with acute infection is ~ 0.6% [6]. Acute infection is most common among individuals in late adolescence, the primary blood donor age [39]

^HHV-8 seroprevalence in Uganda among late adolescence (primary blood donor age) is 36% [40]. The prevalence among recipients is ~ 50% [5]. There is an excess risk of HHV-8 seroconversion of 2.3% when transfused HHV-8 positive blood [5]

^∞^Malaria donor prevalence of 5% is a conservative estimate from data in Uganda [41]

^≡^Bacterial contamination prevalence derived from previous [42] and ongoing studies in Uganda of blood donors

+Expected number of infections in a population with no prior immunity

Figure 3 shows study power to detect a statistical difference in cumulative incidence of at least one TTI by 10 weeks between the intervention and control arms at varying levels of efficacy (*y*-axis; 50–90%) and cumulative incidence in the control arm (*x*-axis; 1–10%). Assuming a cumulative incidence of 3.7% in the control, an efficacy of 80% Mirasol PRT treatment (similar to the AIMS trial [29]), non-differential loss to follow-up of 15% by 10 weeks, we have 97% power to detect a statistically significant difference in cumulative TTI incidence between study arms (two-sided alpha = 0.05). Power to detect significant differences in cumulative incidence of malaria is 64%, viral infections 49%, and bacterial infections 51%.

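### The interim look is triggered by 1000 transfusions in one section and 1000 enrolled subjects in another; the stated boundaries and 49% interim power fit about 1000 participants, not 1000 transfusions

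*Protocol article*

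**What the plan says.** The protocol article describes the interim trigger twice.

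- Stopping rules: the efficacy look takes place "when 10-week outcome data are available for the first 1000 randomized transfusions".
- Study power calculations: "There will be an interim analysis after 1000 study subjects have been enrolled". The reader is then pointed to the stopping rules.

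Two other statements bear on the unit.

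- Randomization: "Participants may only be enrolled and randomized once". All later transfusions follow the assigned arm.
- Study power calculations: "We anticipate that participants will receive 1.5 units of WB on average", with about half of participants expected to have two or more transfusions.

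The operating figures are in Stopping rules. For the Lan-DeMets form of the O'Brien-Fleming procedure, "the alpha level will be set to 0.00304, with the final testing alpha set at 0.04895 to maintain the overall alpha of 0.05". At 80% efficacy, "there is 49% power for this interim criterion to be met".

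**The concern.** The two triggers differ in unit (transfusions or subjects) and, on their face, in timing (10-week data in hand or enrolment reached). A randomised transfusion does not exist in this design. Since participants are expected to receive more than one unit on average, the two counts cannot be exchanged.

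The trigger decides when unblinded efficacy data go to the DSMB, and the futility calculation follows from the same look. The boundary levels are given as fixed numbers, so they are right only at the information fraction for which they were computed. If the literal trigger gives another fraction, neither the levels nor the stated interim power belong to it.

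This has practical weight. Trial status reports more than 700 participants recruited. At 1.5 units each that is already about 700 × 1.5 = 1050 units, while 1000 participants had not been reached. The article does not say how many of these had 10-week data.

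**Working it through.** **Inputs.** From Study power calculations: control incidence 3.7%; 80% efficacy, so 0.2 × 3.7% = 0.74% with Mirasol; 15% loss; 1000 per arm; "two-sided alpha = 0.05"; 1.5 units per participant. From Stopping rules: 0.00304, 0.04895 and 49%. Assumption: one unit is one transfusion.

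**1. Which information fraction do the levels belong to?** The two-sided O'Brien-Fleming-type spending function is α(t) = 4 × [1 − Φ(2.2414/√t)].

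- t = 0.50: 2.2414/√0.50 = 3.170, so α = 0.00305. The matching final level is 0.0490.
- t = 1/3: 2.2414/√(1/3) = 3.882, so α = 0.00021. The matching final level is 0.0499.

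The stated pair agrees with t = 0.50 to within 0.00005. Solving for 0.00304 gives t = 0.4997. The levels therefore assume half the information: 1000/2000 or, with 15% loss throughout, 850/1700.

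**2. Which sample size does 49% belong to?** The article gives no power formula, so I used the normal approximation for two proportions in three forms. With d = p1 − p2 and p̄ their mean:

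- s0 = √[2p̄(1 − p̄)/n] and s1 = √{[p1(1 − p1) + p2(1 − p2)]/n}
- pooled: Φ[(d − z·s0)/s1]
- unpooled: Φ[d/s1 − z]
- continuity-corrected: Φ[(d − 1/n − z·s0)/s1]

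Here d = 0.0296, p̄ = 0.0222, and z = 2.964 for a two-sided 0.00304.

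| Participants per arm | Meaning | Corrected | Pooled | Unpooled |
|---|---|---|---|---|
| 500 | 1000 with outcomes | 49.9% | 58.5% | 59.1% |
| 425 | 1000 randomised, 15% lost | 39.4% | 48.6% | 49.2% |
| 333 | 1000 transfusions, no loss | 26.2% | 35.5% | 36.0% |
| 283 | 1000 transfusions, 15% lost | 19.4% | 28.2% | 28.7% |

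Worked line for 500 per arm, corrected: s0 = 0.00932 and s1 = 0.00927; (0.0296 − 0.0020 − 2.964 × 0.00932)/0.00927 is approximately 0, so power is about 50%.

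The stated 49% is reproduced in two ways, both with 1000 participants. The corrected form at 500 per arm is the better match to the article's other powers. At 850 per arm and alpha 0.05 it gives 97.9% overall, 65.7% for malaria (1.5%), 50.6% for bacteria (1.13%) and 47.8% for viral infections, against the stated 97%, 64%, 51% and 49%. The viral rate is (0.2 + 0.5 + 0.4 + (6.8 + 12.4)/2)/1000 = 1.07%. The pooled form gives about 75%, 62% and 60% for the three components.

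**3. What does the literal trigger give?** 1000/1.5 is about 667 participants, 333 per arm, or 283 per arm after 15% loss. The fraction is 667/2000, about 1/3. Interim power at 0.00304 is 19% to 36% from the table. The most favourable other form tried, arcsine at 333 per arm, gives 42%, still short of 49%. If all 667 were evaluable against 1700 at the end, the fraction would be 0.392 and the spending level 0.00069.

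**4. What happens to type I error?** Under the null the two statistics are bivariate normal with correlation √t. Using 0.00304 and then 0.04895:

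- t = 0.50: overall two-sided alpha 0.0499
- t = 1/3: overall two-sided alpha 0.0506

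To hold 0.05 after spending 0.00304 at t = 1/3, the final level would have to be 0.0483 rather than 0.04895.

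**5. Does it matter whether lost participants count?** If the 1000 are randomised participants, lost ones included, the fraction is 850/1700 = 0.50. If they are 1000 evaluable participants against 1700 evaluable at the end, it is 1000/1700 = 0.588, and the levels become 0.0069 and 0.0478.

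**The case against.** The strongest reply is that this is one wrong noun which the rest of the text corrects. The power section speaks of subjects, the trial size is 2000, and the levels point to half of that. A DSMB with the whole article would be unlikely to look at about 667 participants. The enrolment sentence is a short pointer that defers to the stopping rules, so the difference in timing is weaker than the difference in unit. Much of this stands: 1000 participants is very probably what was meant. It does not make the rule correct as written, and the section to which the reader is sent is the one with the wrong unit.

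A reader might infer from the roughly 15-fold gap between 0.00304 and 0.00021 that control of the overall error rate breaks down. The calculation does not support that. The ratio compares nominal levels at a single look, and overall alpha rises only to 0.0506.

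A reader might also infer that 49% fits nothing but 1000 participants with complete outcomes. It also fits 1000 randomised with 850 evaluable, if no continuity correction is used. Both are counts of participants, and the article does not say which was intended.

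Recomputing boundaries at the fraction reached is often left to the analysis plan, and the named method allows it. The absence of that detail is not the point here; the inconsistent trigger is.

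**Conclusion.** The concern holds. The stopping rule names a unit that is not randomised and disagrees with the power section, and its levels and interim power belong to about 1000 participants at 50% information. Under the literal wording the fraction is about 1/3, the spending function gives 0.00021, and interim power is about 19% to 36% by the risk-difference normal approximations. The effect on type I error is small (0.0506 against 0.05). What is at stake is mainly when the look takes place, and a quoted power that does not apply to it.

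The figure of 667 participants rests on equating a unit with a transfusion and on the planned mean of 1.5. The power range rests on formulas I chose, because the article states none. The conclusion that 1000 transfusions does not yield 49% held in every form tried.

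**What to change.** Use one trigger in both Study power calculations and Stopping rules: *when the first 1000 randomised participants have completed or passed the 10-week visit*. Add a sentence saying whether participants lost to follow-up count towards the 1000. Describe 0.00304 and 0.04895 as the values at 50% information, and state that the boundaries will be recomputed from the Lan-DeMets function if the fraction actually reached differs.

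The cost is a rewording of two sentences and a short addition. Nothing in the design, sample size or conduct changes. It should be settled before any unblinded data are tabulated, so that the timing of the look cannot appear to have been chosen afterwards.
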